## Abstract

**Background:**

Marfan syndrome (MFS) is one of the most common systemic disorders of connective tissue with the incidence of approximately 2-3 per 10 000 individuals. Aortic disease, leading to progressive aneurysmal dilatation and dissection is the main cause of morbidity and mortality of Marfan patients. Current treatment (e.g. beta blockers and elective surgery) does postpone but cannot prevent aortic complications in these patients. Recent studies have found Transforming Growth Factor β (TGF β) to be involved in the aortic aneurysm formation. Losartan, an Angiotensin II type 1 receptor blocker inhibits TGFβ in a mouse model of Marfan syndrome leading to inhibition of aortic growth. The main objective of this trial is to assess whether losartan treatment leads to a clinically relevant decrease of aortic dilatation in adult patients with Marfan syndrome.

**Methods/Design:**

COMPARE study (COzaar in Marfan Patients Reduces aortic Enlargement) is an open-label, randomized, controlled trial with blinded end-points. Treatment with losartan will be compared with no additional treatment after 3 years of follow-up. We will enroll 330 patients with MFS who will be randomly assigned to receive losartan or not. Patients taking beta-blockers will continue taking their standard treatment. The primary end-point is the largest change in aortic diameter at any aortic level measured by means of MRI. Secondary end-points are change in mortality, incidence of dissection, elective aortic surgery, aortic volume, aortic stiffness and ventricular function. We will also investigate gene and protein expression change in the skin under losartan therapy and create prediction models for losartan-treatment response and aortic dilatation.

**Discussion:**

The COMPARE study will provide important evidence of effects of losartan treatment in adult Marfan patient population. We expect losartan to significantly reduce the occurrence and progression of aortic dilatation. This trial investigates a wide spectrum of clinical, genetic and biochemical effects of losartan aiming to provide further insight in the pathogenesis and treatment of Marfan syndrome.

**Trial registration:**

Netherlands Trial Register NTR1423.

## Background

Marfan syndrome (MFS) is one of the most common systemic disorders of connective tissue with the incidence of approximately 2-3 per 10 000 individuals [1]. MFS is an autosomal dominant disorder with cardinal clinical features involving the cardiovascular, ocular and skeletal systems. MFS is a clinical diagnosis which is made when an index patient fulfils major criteria in two systems and has an involvement in a third system according to Ghent criteria[2]. Clinical features involve ocular lens luxation, long bone overgrowth, lung emphysema and cardiovascular complications including aortic aneurysm and mitral valve prolaps.

Aortic disease, leading to progressive aneurysmal dilatation and dissection is the main cause of morbidity and mortality of Marfan patients. Routine monitoring of aortic growth is necessary to detect and quantify the progression of aortic dilatation, in combination with β adrenergic receptor antagonist therapy to slow down aortic growth[3]. Prophylactic aortic repair is indicated when dilatation reaches sufficient size to threaten aortic dissection[4]. Current therapy has improved life expectancy of this group of patients. However, it is important to note that even treated patients continue to have abnormal aortic growth. Moreover, dissection may occur in not-operated parts of the aorta. Therefore, current treatment does postpone but cannot prevent aortic complications in these patients.

MFS is caused by mutations in FBN1, the gene encoding fibrillin-1, which is the main component of the extracellular matrix[5]. Fibrillin-1 was initially thought to play primarily a structural role in connective tissue. Some of the features of Marfan syndrome like lens luxation can be explained by weakness of connective tissue due to a defect fibrilline-1. However, this hypothesis was insufficient to clarify the pathogenesis of other features, like bone overgrowth and facial appearance in these patients. The additional role of fibrilline-1 as a regulator of a cytokine named Transforming Growth Factor β (TGF-β) emerged [6-8]. TGF-β is a growth factor which is involved in many biological processes including cellular proliferation, deposition of the extracellular matrix, differentiation, apoptosis etc [6-9]. In a mouse model of MFS, increased TGF-β signaling appeared to play a causal role in many phenotypic features of MFS like progressive aortic root dilatation, defect lung development resulting in bullae formation and failed muscle regeneration [6,7,9,10].

These new insights in the pathophysiology of MFS are a major step forward in the understanding of connective tissue disorders, offering new opportunities for treatment of these patients.

Angiotensin II type 1 receptor (AT1) blocker losartan was found to be potentially useful in MFS because it leads to antagonism of TGF-β in animal models of chronic renal insufficiency and cardiomyopathy[11]. Numerous studies describe the ability of losartan to achieve a clinically relevant inhibition of TGFβ. This led to an assumption that losartan can treat or even prevent some features of MSF. Promising preliminary results on aortic dilatation inhibition have been achieved in a small observational study with children with severe MFS[10].

MFS is a very pleiotropic disorder. Up-till now no parameters of genotype-phenotype correlation have been found [12]. Neither the location of the mutation nor the type of aminoacid altered nor even the family presentation are sufficient to predict the phenotype both among as within the affected families[13]. These findings suggest that other genes may be involved in the pathogenesis modifying the phenotype.

## Methods/Design

The COMPARE trial is an open-label, randomized, controlled trial with blinded end-points. Treatment with losartan will be compared with no additional treatment after 3 years of follow-up. We will enroll 330 patients with MFS who will be randomly assigned to receive losartan or not. Patients taking beta-blockers will continue taking their standard treatment. This multi-center study will be conducted in four academic centers in the Netherlands: Academic Medical Center in Amsterdam, University Medical Center St. Radboud in Nijmegen, University Medical Center Groningen and Leiden University Medical Center. A flow chart of the study design is shown in the Figure 1.

**Figure 1 F1:**
[figure not shown]
**Flow of participants, COMPARE study**.

### Objectives

#### Primary objective

The main objective of this study is to assess whether losartan reduces aortic dilatation at any aortic level, from the aortic root to the bifurcation. The primary end-point is the largest aortic diameter at any level measured by means of Magnetic Resonance Angiogram (MRA). If MRA is contraindicated, a Computed Tomography (CT) will be performed.

We will therefore test the null hypothesis that there is no significant difference in aortic diameters after 3 years of follow-up in the treated and the control groups. MRA's will be assessed by a person who is blinded for patient's treatment.

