## Statistical considerations

Mean change in aortic diameter in patients with MFS is 0.9-1.5 mm/year[4]. Sample size calculation is based on the primary endpoint (rate of change of aortic diameter). The expected difference between two groups is 0.5 mm/year with a standard deviation of 1.5 mm (2-sided α = 0.05; β = 0.2). Based on these assumptions we calculated that 286 patients are required. To compensate for an estimated 20% drop-out, the inclusion of at least 330 patients is advised.

Primary analyses will be performed on an intention to treat basis. To evaluate the primary end-point a covariate analysis of the diameter change will be used in two groups (no treatment vs losartan) at baseline and after 3 years. Covariate analyses will be also used for the following secondary points: aortic volume, distensibility, pulse-wave velocity, left and right ventricle volumes. "Safety parameters" (i.e. mortality, dissections, surgery) will be evaluated by means of a X^2 ^test.

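### The primary endpoint is the largest growth at any level in the abstract but the largest diameter in the objectives, and the sample-size SD is tied to neither

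*Protocol article*

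**What the plan says.** Three places in the protocol article describe the primary endpoint.

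- **Abstract, Methods/Design:** "The primary end-point is the largest change in aortic diameter at any aortic level measured by means of MRI". The quantity is a change, taken at whichever level changed most.
- **Objectives, Primary objective:** "The primary end-point is the largest aortic diameter at any level measured by means of Magnetic Resonance Angiogram (MRA". The quantity is a diameter, taken at the widest level. The null hypothesis follows suit: "there is no significant difference in aortic diameters after 3 years of follow-up in the treated and the control groups".
- **Statistical considerations:** "Sample size calculation is based on the primary endpoint (rate of change of aortic diameter", and for the analysis "To evaluate the primary end-point a covariate analysis of the diameter change will be used in two groups". The quantity is a change or its rate. No level is named.

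The sample-size inputs are "The expected difference between two groups is 0.5 mm/year", "with a standard deviation of 1.5 mm" and "2-sided α = 0.05; β = 0.2". They lead to 286 patients before drop-out. The difference carries a time unit and the SD does not.

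**The concern.** A primary endpoint on a multi-level structure needs a quantity (diameter or change) and a rule for the level. The abstract and the objectives disagree on both, and the statistical section settles only the first. The level that grew most is known only after the second scan and may be anywhere in the aorta. In many patients the widest level will be the one that was already widest at baseline.

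The primary result is therefore not determined by the scans alone. Treatment is open-label, and although the scan reader is blinded, blinded reading does not decide which derived variable is primary. The power statement is affected too, since a difference and an SD belong to one variable and the article does not say which.

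**Working it through.** **1. Do the wordings give different values for one patient?** Take two levels, with illustrative diameters:

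- root 45 → 46 mm, change 46 − 45 = +1 mm
- descending aorta 28 → 32 mm, change 32 − 28 = +4 mm

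The largest change is +4 mm, at the descending aorta. The largest diameter is 45 mm at baseline and 46 mm at 3 years, so its change is +1 mm. Over 3 years these are 1.33 and 0.33 mm/year, a gap of 1.0 mm/year in one patient. The planned difference between arms is 0.5 mm/year.

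**2. Which variable does 286 fit?** Inputs from Statistical considerations: difference 0.5, SD 1.5, two-sided α 0.05, power 0.80. Allocation is 1:1 (Exclusion criteria section).

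n per arm = 2 × (1.960 + 0.842)² × (1.5 / 0.5)² = 2 × 7.85 × 9 ≈ 141.3, so 142 per arm and 284 in total. The t-test version gives 142.2, so 143 per arm and 286 in total. The article's figure reproduces (power 0.80 at 143 per arm).

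This requires difference and SD in the same unit, mm/year. As a total over 3 years it is a difference of 1.5 mm with an SD of 4.5 mm, which gives 284 again. If 1.5 mm were the SD of the total 3-year change, n per arm = 2 × 7.85 × (1.5 / 1.5)² ≈ 15.7, so 16 per arm and 32 in total, which does not match.

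The formula does not reveal the level. It fits any variable with a mean difference of 0.5 mm/year and an SD of 1.5 mm/year.

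**3. What if the objectives' wording were taken literally?** Compare the largest diameter at 3 years between arms, unadjusted, with a difference of 0.5 × 3 = 1.5 mm. The between-patient SD is not in the article, so a range is assumed:

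| Assumed SD (mm) | Total N for 80% power | Power at 143 per arm |
|---|---|---|
| 3 | 126 | 0.99 |
| 4 | 224 | 0.89 |
| 5 | 350 | 0.72 |
| 6 | 504 | 0.56 |
| 8 | 894 | 0.35 |

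**4. Can the choice change the trial's answer?** This is an illustrative simulation, and its inputs are assumptions: 6 levels, root widest on average (44 mm), annual change with mean 0.9 and SD 1.5 mm/year at every level, between-level correlation 0.3, 143 per arm, 1,500 runs. Entries are the proportion of trials with p < 0.05.

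| Effect of 0.5 mm/year acts on | Largest change at any level | Change at the widest baseline level | Largest 3-year diameter, unadjusted | Same, adjusted for baseline maximum |
|---|---|---|---|---|
| all levels | 0.95 | 0.80 | 0.58 | 0.82 |
| root only | 0.06 | 0.78 | 0.51 | 0.75 |
| all levels except the root | 0.83 | 0.05 | 0.05 | 0.06 |

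Baseline adjustment brings diameter and change at the widest level close together. It does not bring either close to the largest change at any level.

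**The case against.** The strongest reply is that the conflict is smaller than it looks, and much of that stands.

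- **A reader might count three incompatible endpoints.** With one final scan at a fixed 3 years (Follow-up), rate and change at the same level differ only by a factor of 3. If baseline diameter is a covariate, analysing change or the 3-year diameter at the same level gives the same treatment effect. The stated aim of reducing dilatation, and the planned analysis, both point to change. Two discrepancies remain: the level rule, which adjustment cannot repair, and the objectives' use of diameter where change seems meant. The statistical section's silence on level is not a third definition, but it means that section cannot resolve the first discrepancy.
- **A reader might infer that a maximum over noisy levels biases the comparison.** It raises apparent growth within each arm, but the reader is blinded and the rule is the same in both arms. In a check with 1 mm of reading error, the test on the maximum had a type I error of 0.052 with 3 levels and with 6.
- **A reader might conclude that the stated 80% power is wrong.** The documents do not show this. With an effect at the root only, power on the largest change was 6% under the assumptions above. It was 54–69% under another set (3-year root change with mean 3.6 and SD 4.5 mm, other levels mean 1.5 and SD 1.5 mm). The answer follows from inputs that the article does not give.
- **A reader might object that eligible patients with one prosthesis have fewer native levels.** How such segments are measured is a detail that a full protocol or analysis plan commonly holds, so it is not counted here.

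The full protocol or analysis plan may also settle on one definition. That would not make the article's own statements agree. The point rests on conflicting text, not on missing detail.

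**Conclusion.** The point holds, and the primary endpoint is wrong as written. The abstract and the objectives name different variables, the statistical section names no level, and no section says which governs. In the worked patient the two rules give +4 mm and +1 mm. This conclusion needs only the text.

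The 286 reproduces for a difference of 0.5 mm/year with an SD of 1.5 mm/year, and the article does not attach that SD to either definition. The simulation shows that the choice can reverse the primary result under some patterns of effect. Its figures, and those in the SD table, rest on assumed inputs and do not estimate this trial's power.

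**What to change.** Before any 3-year scan is analysed, state one primary endpoint in identical words in the abstract, the Primary objective section and Statistical considerations. It should give:

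- the quantity: change in diameter from baseline to 3 years, in mm/year;
- one rule for selecting the level, consistent with the stated objective of covering the whole aorta;
- the null hypothesis as no difference between arms in mean change;
- the SD of that variable with its time unit, and a power or sample-size statement restated to match.

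Report the other definition as secondary. The level rule is the sponsor's choice. A rule that fixes the root first is possible but not required, and it would narrow the stated objective.

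The cost is amendment wording and one recalculation, with the same scans and the same blinded reader. Enrolment began in March 2008, so on the planned schedule no final scan fell due before March 2011. The article reports 230 of 330 patients enrolled by October 2009, which left time to settle this without reference to outcome data.

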#### Secondary objectives

The secondary objectives are to asses whether losartan influences:

• Mortality, incidence of newly diagnosed dissection in any main vessel and incidence of elective aortic surgery combined into one event endpoint

• Aortic volume measured by means of MRA

• Aortic pulse wave velocity (PWV) and distensiblity measured by means of Magnetic Resonance Imaging (MRI)

• Ventricular function measured by means of MRI

#### Objectives of genetic expression studies

This study aims also to provide further understanding of the pathofysiology of MFS. Skin samples will be used as a model of the aortic tissue. We will assess gene expression in the skin samples of the treated patients at three points: at baseline, after four weeks of treatment and after one year of losartan treatment. Genome wide expression will be measured to identify genes the expression of which changes under losartan therapy. The expression analysis is mainly exploratory and will be performed also for pathways involved in the pathogenesis of Marfan syndrome, i.e. TGF-β pathway. Expression panels will be correlated with the rate of aortic dilatation. Results will be used to build prediction models of the losartan-therapy response and to identify genes which may influence the phenotype. Results will be validated in aortic tissue collected from Marfan patients operated in one of the four participating centers.

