### Follow-up

After inclusion the following will be obtained during the baseline investigations (V1):

• Patients medical history

• Echocardiography

• MRI or a CT of the heart and entire aorta

• Blood samples

• Punch skin biopsy

Patients will be evaluated after one, two and three years of treatment by means of echocardiography. After 4 weeks and one year of the treatment an additional skin biopsy will be obtained. At every visit, patient's medical history will be obtained. Date of dissection, operation or death will be carefully noted.

The final assessment will be after 3 years of treatment by means of MRI.

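### Skin expression is followed in losartan patients only, so the planned results cannot by themselves separate losartan response from prognosis, or drug effect from time

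*Protocol article*

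**What the plan says.** The section on objectives of genetic expression studies sets the sampling: "We will assess gene expression in the skin samples of the treated patients at three points". These are before losartan starts, four weeks into treatment and one year into treatment. It then gives three uses for the data:

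- Change on the drug: "Genome wide expression will be measured to identify genes the expression of which changes under losartan therapy".
- Relation to outcome: "Expression panels will be correlated with the rate of aortic dilatation".
- Prediction: "Results will be used to build prediction models of the losartan-therapy response and to identify genes which may influence the phenotype".

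The same section says "The expression analysis is mainly exploratory" and plans validation in aortic tissue from Marfan patients operated on at the participating centres. The abstract (Methods/Design) also announces prediction models, both for losartan response and for aortic dilatation.

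Two other places bear on the point. The Follow-up section lists "Punch skin biopsy" among the baseline (V1) investigations, with no limit to one arm, and ties the two later biopsies to time on treatment. The paragraph after the exclusion criteria describes 1:1 randomisation to losartan or no losartan.

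**The concern.** Response to losartan is the difference between a patient's aortic growth on the drug and the growth that patient would have had without it. Treated patients alone show only the first of these. A panel that goes with slow growth in the losartan arm may mark patients who respond, or patients who would have grown slowly anyway. The reverse can also happen: a marker of poor prognosis that also predicts benefit may show no association in the treated arm.

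Finding genes that change on losartan has a parallel problem. A change from baseline in one arm contains any drug effect together with time, the effect of repeated biopsy, and assay batch.

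What is at stake is the meaning of two announced products of the sub-study: the response models and the list of losartan-responsive genes.

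**Working it through.** **Inputs from the protocol article (Statistical considerations, unless noted).** Difference 0.5 mm/year; SD 1.5 mm; two-sided α 0.05; power 0.80; 286 patients required; 330 to be enrolled; 20% drop-out; 1:1 allocation (paragraph after the exclusion criteria). No sample size or effect size is given for the expression study.

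**The plan's own figure.** Normal approximation: n per arm = 2 × (1.96 + 0.842)² × 1.5² / 0.5² ≈ 141.3, so 142 per arm and 284 in total. The t-test version gives 142.25, so 143 per arm and 286 in total. The stated 286 is reproduced. This reads the SD as 1.5 mm/year.

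**Number of treated patients.** At most 330 / 2 = 165. After 20% drop-out, 165 × 0.8 = 132. The article does not say how many treated patients will be biopsied, so fewer is possible.

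**1. What a treated-only slope estimates.** Write growth = a + b·arm + c·marker + d·(arm × marker), with arm = 1 for losartan. In losartan patients the slope on the marker is c + d. Here c is prognosis and d is the modification of the drug's effect. Without controls the two cannot be separated.

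**2. How often a purely prognostic marker (d = 0) is flagged.** By Fisher z, power = Φ(atanh(r) × √(n − 3) − z_crit). The correlations r are assumptions.

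| Assumed r (absolute) | n = 132, single test at 0.05 | n = 165, single test at 0.05 |
|---|---|---|
| 0.1 | 21% | 25% |
| 0.2 | 63% | 73% |
| 0.3 | 94% | 98% |

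Worked cell: r = 0.3, n = 165 gives 0.3095 × √162 = 3.94, and Φ(3.94 − 1.96) = 0.976. With n = 132: 0.3095 × √129 = 3.52, and Φ(3.52 − 1.96) = 0.940.

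Multiplicity correction changes this sharply. At r = 0.3, Bonferroni over an assumed 1,000 genes gives 29% (n = 132) and 45% (n = 165). Over an assumed 20,000 genes it gives 12% and 22%.

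**3. Treated-only against two-arm analysis.** Simulation, 2,000 runs, 143 per arm, mean effect −0.5 mm/year, SD 1.5. The marker effects (mm/year per SD of the marker) are assumptions.

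| Prognosis c | Interaction d | Treated-only slope; rejected | Two-arm interaction estimate; rejected |
|---|---|---|---|
| 0.3 | 0 | 0.30; 68% | 0.00; 6% |
| 0.5 | 0 | 0.50; 99% | 0.00; 4% |
| 0.3 | −0.3 | 0.00; 5% | −0.30; 40% |

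The first two rows are false response markers. A slope of 0.3 on an SD of 1.5 is a correlation of 0.2, so the 68% agrees with step 2. The third row is a true predictor that the treated-only analysis misses.

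**4. Change over time with no drug effect.** Same runs, 143 per arm, assumed drift in SDs of the change.

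| Drift | Pre-post test, treated only | Between-arm test of change |
|---|---|---|
| 0.1 | 21% | 5% |
| 0.2 | 67% | 5% |
| 0.3 | 94% | 5% |

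**The case against.** The best case on the other side has four parts.

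**The text restricts less than it seems to.** Only the three-point serial assessment is explicitly confined to treated patients. The sentences on correlation and modelling name no population and do not rule out an interaction term, and a dilatation model has no evident reason to exclude controls. Baseline skin in both arms with serial skin in the treated arm is a coherent reading, and model details commonly sit in a fuller document. This stands in part. A reader might infer that control biopsies are in storage and simply unused. The article does not establish that: it neither limits the V1 biopsy to one arm nor mentions storage or assay of control skin. It does name treated patients as those assessed and builds the response models on the results, and no analysis plan can recover control data that were never assayed.

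**The work is exploratory.** It is labelled so, and validation is planned. This lowers the weight of the point. It does not remove it, because the label excuses low power and multiplicity, but not a quantity the data cannot identify. Aortic tissue from operated patients is not a randomised untreated comparison. A reader might also infer that expression would be used to choose who gets losartan; the article proposes no such use.

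**The error rates depend on assumptions.** They do. A figure above 95% needs a correlation of 0.3, one test at 0.05 and almost no drop-out. It does not carry over to a corrected genome-wide screen.

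**The remedy is partial.** Control skin from V1 can help only with baseline markers, and the interaction test is weak, at about 40% power in the example above. Both are true. Low power for the right question is a reason for cautious conclusions, not for replacing it with a different question.

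**Conclusion.** The point holds for the expression sub-study only. Followed as written, the treated-only assessment cannot support the term losartan response, nor attribute changes in expression to losartan. This follows from the design and needs no numerical assumption.

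Its size does need assumptions. For a single test at 0.05 in 132 to 165 treated patients, a purely prognostic marker is flagged in about 63% to 73% of cases at a correlation of 0.2, and in about 94% to 98% at 0.3. The rates are much lower under genome-wide correction. With a drift of 0.1 to 0.3 SD and no drug effect, the uncontrolled pre-post test rejects in 21% to 94% of runs.

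A reader might take this as a flaw in the trial's main evidence. It is not: the primary and secondary endpoints compare the randomised arms and do not use the skin data.

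**What to change.** 1. **Reconcile the two sections.** The genetic expression objectives and the Follow-up section should state the same thing about whose biopsies are taken, at which visits, and whose are assayed. Cost: wording.
2. **If baseline skin exists in both arms,** assay a limited panel (candidate genes and the TGF-β pathway) in controls as well. Fit growth on arm, baseline expression and arm × expression, and call a marker predictive of response only on the interaction term. Cost: the control assays, and low power for the interaction, which should be acknowledged.
3. **If control skin does not exist or will not be assayed,** restate the models, in the abstract as well, as predicting dilatation within losartan-treated patients. Cost: wording.
4. **In either case,** describe the 4-week and 1-year expression changes as uncontrolled changes during losartan treatment. V1 control samples cannot correct them. Cost: wording.
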